Cognitive Behavioural Therapy (CBT) in its current form is not suitable for persons from the non-western cultural background [10–13]. Culturally adapted Cognitive Behavioural Therapy (CaCBT) is an evidence-based practice [10, 14–18]. CaCBT is more effective than standard CBT and can reduce dropouts from therapy compared with standard CBT [19, 20]. Thus, CaCBT can increase access to mental health services and improve outcomes for immigrant, refugee and ethno-cultural and racialized populations [21–23]. Adapting CBT for growing SA populations in Canada will ensure equitable access to effective and culturally appropriate interventions. Accordingly, this study proposes to develop and evaluate CaCBT for depression and anxiety among SA populations in Canada.

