##### Measurements

Assessments will be carried out at baseline after therapy has been completed (12 weeks from baseline) and at follow-up (36 weeks from baseline) by raters blinded to group allocation. The primary outcome, the effectiveness of the psychotherapy addressing levels of depression and anxiety, will be measured using the HADS Depression subscale [37]. HADS is a 14-item, self-assessment scale designed to measure anxiety and depression. The maximum score is 21 for depression and 21 for anxiety. A score of 8–10 suggests the presence of the borderline cases, while a score of 11–21 indicates probable cases. Secondary outcomes, including somatic symptoms, disability, feasibility, acceptability and satisfaction, will also be measured. The Bradford Somatic Inventory (BSI) enquires about a wide range of somatic symptoms during the previous month and has 45 items. Scores above 21 indicate depression [38]. Disability will be measured using the World Health Organization’s Disability Assessment Schedule 2.0 (WHODAS) [39]. This scale assesses disability due to physical and psychological problems and has been used extensively in various research settings. Feasibility will be measured through engagement, recruitment and retention of participants. Acceptability will be measured through feedback from participants and therapists. Participants will also be asked to report their satisfaction by responding to the Verona Service Satisfaction Scale [40]. The Working Alliance Inventory (WAI) [41] will be used to measure therapeutic alliance.

A questionnaire adapted from Beecham and Knapp’s [42] costing psychiatric interventions measurement protocol will be used to ascertain health and social service utilization relevant from the perspective of the health system and participant perspectives. The questionnaire filled out by participants at baseline will inquire on service utilization in the past 6 months. The questionnaires at 3 and 9 months post-treatment will inquire about service utilization in the past 3 and 6 months. Information on outpatient and emergency department visits, hospitalizations and medications, visits to community organizations and receipt of social services will be collected. Participant out-of-pocket costs for seeking health and social services will also be considered and include drug co-payments, direct payments to professionals not covered by public insurance plan, cost related to transportation and time spent by patients while consulting.

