
For the economic evaluation, an incremental cost-effectiveness analysis will be carried out to estimate the cost-effectiveness (C/E) ratio associated with the CaCBT programme according to published guidelines [53, 54]. The costs incurred during the study period (3 and 9 months) will be accounted for in both experimental arms. Effectiveness will be considered based on a 25% decrease in HADS and improvement (yes/no) in WHODAS scores between baseline and the 3-month and 9-month observation periods. The C/E ratio will be calculated for the 3-month and 9-month observation periods as follows: [average costs (CaCBT group) – average costs (control group)]/[# of improvements in CaCBT group − # of improvements in control group]. This will report the additional average costs associated with one improved case associated with the programme. Treatment groups will be compared with respect to baseline characteristics (age, sex) as well as scores on the HADS, WHODAS and health service utilization in the previous 6 months such as the number of outpatient and emergency department visits and hospitalizations and follow-up and adherence to programme. This will elucidate whether these factors will need to be considered in the analyses and interpretation of C/E results. Sensitivity analyses will also be carried out to test the robustness of the results.

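### The cost-effectiveness ratio is unadjusted, an observed comparison of the arms guides whether covariates enter, and adherence and follow-up are listed with the baseline factors

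*Protocol article*

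**What the plan says.** All of this is in the Protocol article, Phase 2.

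- **Estimator.** Under Statistical analyses, the ratio is built from "average costs (CaCBT group) – average costs (control group)]/[# of improvements in CaCBT group − # of improvements in control group" (outer brackets omitted). It contains no covariates.
- **Comparison of arms.** The same paragraph continues: "Treatment groups will be compared with respect to baseline characteristics (age, sex) as well as scores on the HADS, WHODAS", then "health service utilization in the previous 6 months such as the number of outpatient and emergency department visits and hospitalizations", and closes the list with "and follow-up and adherence to programme".
- **Purpose of the comparison.** "This will elucidate whether these factors will need to be considered in the analyses and interpretation of C/E results". The next sentence promises sensitivity analyses without describing them.
- **Data available.** Under Measurements: "The questionnaire filled out by participants at baseline will inquire on service utilization in the past 6 months". HADS and WHODAS are also assessed at baseline.
- **Expected effect on retention.** The Background says that the adapted therapy "can reduce dropouts from therapy compared with standard CBT", and the Discussion says that fewer dropouts are possible in this trial.
- **Contrast.** The clinical mixed model in the same section names gender and baseline HADS as covariates in advance.

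**The concern.** In a randomised trial, the reason to adjust for a baseline variable is that it predicts the outcome. Whether the arms happen to differ on it is a poor guide, because a strong predictor is worth including even when the arms look balanced. Prior service use is a natural predictor of later service use, and so of cost. A plan that waits for the observed comparison will often leave that information unused.

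The list also mixes two kinds of variable. Age, sex, HADS, WHODAS and prior service use are fixed before allocation. Follow-up and adherence arise afterwards, and the article expects the intervention to affect dropout. Retention is also one of its measures of feasibility, a secondary outcome, and sessions delivered are part of programme cost. Conditioning on adherence could therefore remove part of the cost or benefit that the ratio is meant to capture.

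Finally, follow-up and adherence can be compared only once post-randomisation data exist. A decision that rests on the whole list therefore comes late, when cost and outcome data may already be in hand. The economic evaluation is a stated secondary objective, so its covariate set should not be settled at that stage.

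**Working it through.** **The plan's own figures.** The article gives no figure for the economic analysis. Its clinical sample size is the only one to reproduce, and it is not in dispute. With d = 0.68, 90% power and 5% significance (taken as two-sided), 2 × (1.960 + 1.282)² / 0.68² = 45.5, so 46 per group; the t-test version gives 46.4, so 47. The article states 48. Allowing 30% attrition, 96 / 0.70 = 137.1, or 138 as two groups of 69; the article states 140. If 30% of 140 are lost, 98 remain, or 49 per arm.

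**Precision forgone.** The documents give no cost SD and no correlation r between baseline and follow-up cost, so r is assumed to lie between 0.3 and 0.7. Always adjusting multiplies the standard error (SE) of the cost difference by √(1 − r²):

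- r = 0.3: √0.91 = 0.954, a 5% reduction
- r = 0.5: √0.75 = 0.866, a 13% reduction
- r = 0.7: √0.51 = 0.714, a 29% reduction

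**What an imbalance-triggered rule would recover.** The article sets no threshold, so p < 0.05 on the baseline comparison is used here as an illustration only. Simulation with normal data, 70 per arm and 8,000 trials per setting gave these SEs, in SD units:

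| r | Unadjusted | Adjust if p < 0.05 | Always adjust |
|---|---|---|---|
| 0.3 | 0.168 | 0.167 | 0.162 |
| 0.5 | 0.169 | 0.163 | 0.148 |
| 0.7 | 0.168 | 0.156 | 0.121 |

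The rule triggered in about 5% of trials and cut the SE by about 1%, 3% and 7%. The pattern was similar with 49 per arm.

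**A single unlucky draw.** If the arms differ at baseline by z = 1.5 (p = 0.13), the unadjusted cost difference is shifted, given that draw, by r × z of its SE: 0.45, 0.75 and 1.05 for r = 0.3, 0.5 and 0.7. Averaged over randomisations the shift is zero.

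**Adjusting for adherence, if it were done.** Let the arm change adherence by a SD, and let the outcome change by b SD per SD of adherence. The share of a total effect of 0.68 SD that adjustment removes is a × b / 0.68. With a = 0.2 and b = 0.2 this is 0.04 / 0.68 = 6%; with a = 0.6 and b = 0.4 it is 0.24 / 0.68 = 35%. Both a and b are assumed. The effect scale is continuous, whereas the ratio's denominator counts improved cases, so these figures show direction and do not carry over to the ratio.

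**The case against.** The strongest reply is that the article commits to very little. It names no regression, test or cut-off, and it speaks of interpretation as well as analysis. On a plausible reading, the unadjusted ratio is the base case and the comparison informs sensitivity analyses and discussion. Comparing adherence and follow-up by arm is good reporting: sessions attended drive programme cost, and unequal follow-up affects how completely costs are observed. The covariates of a cost regression are also commonly left to an analysis plan, which is not shown here.

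Much of this stands, and it rules out three stronger readings that a reader might infer:

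- **That the plan adjusts only when an imbalance is significant.** No such rule is written for the economic analysis. The p < 0.05 rule above is an illustration.
- **That the plan will adjust for adherence.** The text leaves this open and does not commit to it.
- **That the unadjusted ratio rests on a biased cost difference.** Over randomisations the raw cost difference is unbiased, and its SE already covers chance imbalance. The loss is in precision.

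What does not stand is that this is only missing detail. The article itself says that an observed between-arm comparison will show whether factors need to be considered in the analyses, and it puts baseline and post-randomisation factors in one list under that sentence. An analysis plan that followed the article would inherit both features.

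**Conclusion.** The point holds as a weakness in stated wording. The article fixes an unadjusted ratio, makes the use of covariates depend on how the arms compare, and does not separate follow-up and adherence from the baseline factors. The cost is an avoidable loss of precision, with an SE reduction of about 5% to 29% forgone for assumed correlations of 0.3 to 0.7. There is also room for a data-dependent choice of covariates, and permission, though no commitment, to adjust for variables that the therapy is expected to change. Every magnitude rests on assumed inputs, and no effect on the ratio itself has been computed. The primary clinical analysis is not affected.

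**What to change.** In the economic part of Statistical analyses, replace the sentence that makes consideration of the factors depend on the comparison. State that incremental costs and effects are estimated by regression, adjusted in advance for baseline six-month service use or cost, baseline HADS, baseline WHODAS, gender and site, whatever the observed balance. Gender and site are the stratification factors. Give the unadjusted ratio as a sensitivity analysis.

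In a separate sentence, state that adherence and follow-up are reported descriptively by arm and are not covariates in the treatment comparison. Follow-up may still inform the handling of missing data.

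The cost is a few lines of text. The baseline measures are already planned, so no new data and no change to the sample size are needed.

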### Phase 3: implementation and evaluation of CaCBT

#### Trained therapists working with SA populations to use CaCBT with their clients. Evaluate therapist competence in using CaCBT as well as client satisfaction with the newly developed therapy

##### Methods

The newly developed CaCBT guidelines will be evaluated for enhancing cultural competence among therapists already delivering CBT.

##### Participants

Twenty to thirty therapists not involved in the previous phases will be recruited from participating hospital and community organizations and will attend one full-day training course in CaCBT. We will use a convenient sampling for this recruitment.

##### Measurements

Participants’ knowledge and attitudes will be assessed using pre- and post-training scores on a questionnaire derived from an existing competence in culturally adapted therapy framework [22]. A visual analogue scale will be used to measure their satisfaction and perceived competence before and after training. We will also gather post-training feedback from participating therapists to further enhance our understanding.

##### Analyses

SPSSv25 will be used to measure the change in pre- and post-training scores in therapist competence and their satisfaction using the *t*-test and chi-square test.

## Discussion

Research shows high rates of depression and anxiety among SA Canadians. This group also has lower rates of access to mental health care and has poorer outcomes. There are a number of psychosocial treatments available for depression and anxiety, but to the best of our knowledge, there has been no trial of any evidence-based intervention in this hard-to-reach group in Canada. As such, this is the first trial of culturally adapted CBT for South Asians in North America and Europe. This paper describes the development and testing of culturally adapted CBT. As far as we are aware, this is the first fully powered trial to compare culturally adapted CBT with standard CBT and to conduct an economic evaluation.

The impact of this intervention on service users will be to improve their mental health literacy and improve their self management capabilities through CBT. This may lead to improvement in their well-being and improve their satisfaction with health services as well as improvements in relationships, quality of life and functioning. We are undertaking a detailed process of culturally tailoring this intervention to the specific needs of our target population. This will not only help in improved efficacy but will possibly lead to fewer dropouts and higher satisfaction. The results of this study will be shared widely. Using an integrated dissemination plan, the results of the various stages will be shared through a variety of means including a launch event, webinars, manuscripts and policy reports.

The outcome of this trial will benefit health services in Canada, in terms of helping to reduce the burden of depression and anxiety and provide better care for South Asians. We expect the results to help guide the development of better services and tailor existing services to the needs of other hard-to-reach and vulnerable groups and for other cultural populations.

## Abbreviations

BSI: Bradford Somatic Inventory
CaCBT: Culturally adapted Cognitive Behavioural Therapy
CBT: Cognitive Behavioural Therapy
C/E: Cost-effectiveness
GTA: Greater Toronto Area
HADS: Hospital Anxiety and Depression Scale
LOCF: Last observation carried
MAR: Missing at random
MHCC: Mental Health Commission of Canada
SA: South Asian
WAI: Working Alliance Inventory
WHODAS: World Health Organization Disability Assessment Schedule
